### Cognitive tests

The Montreal Cognitive Assessment (MoCA), the Trail Making Test (TMT) and the Stroop test will be completed by participants to assess cognitive functions. The MoCA is separated into several tasks including visuospatial/executive functioning, naming, memory, attention, language, abstraction, delayed recall and orientation. For example, the participants will be asked to connect numbers and letters in a defined sequence, count backwards from 100 by increments of 7, draw different figures and perform word associations. The MoCA total score (/30) is obtained by summing the scores from each item; a cut-off score below 26 is an indicator of mild cognitive impairment [41]. The TMT, evaluating processing speed and cognitive flexibility, consists of connecting numbers in ascending order (Part 1) and then in connecting numbers and letters in both ascending and alphabetical order (Part 2), as fast as possible [42]. Time needed to complete each part and number of mistakes will be recorded to assess performance. The Stroop test is based on color recognition (i.e., red, green, yellow and blue) with interference in three parts, each composed of 6 lines with 4 items per line (colored sticker or word). The first part is composed of colored stickers (control), the second has colored words (low interference) and the last part has color-words printed in a color not denoted by the name (high interference). For each part, participants will be advised to name the ink color for each word, regardless of the semantic content, as quickly and accurately as possible. The time to complete each part is measured to attribute an interference score used to assess response inhibition, which has been related to cognitive functioning in daily life [43]. The TMT and the Stroop test will be implemented on Inquisit software (Millisecond Software, LCC, Seattle, USA). For SEM analysis, MoCA total scores (/30), TMT time (s) and Stroop interference scores (%) will be considered.

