Most studies investigating CRF were cross-sectional and thus cannot account for the dynamics of these mechanisms, and few studies implemented longitudinal follow-ups. Some longitudinal studies have focused on the psychological dimension and their results are unanimous in asserting that anxiety before treatment was a strong predictor of subsequent CRF in breast cancer patients [26, 36, 37]. At best, these various studies combine only two different dimensions (behavioral and psychological, biological and psychological, clinical and psychological, respectively). Only Bower et al., [5] have led a longitudinal study in breast cancer patients that combines more than two dimensions of CRF, from diagnosis to 18 months post treatment. They have investigated biological, demographic, social, clinical and psychological dimensions. Unfortunately, only baseline results are currently available. They reveal that younger age, lower educational level, lower disease stage and history of childhood maltreatment were found to be significant predictors of CRF.

Recent studies have highlighted the necessity to develop longitudinal and multidimensional researches in order to identify potential mechanisms explaining CRF [8, 38]. Therefore, the purpose of this longitudinal study is to build a biopsychosocial model of CRF by simultaneously investigating anthropometric, clinical, biological, physical, psychological and sociological parameters using structural equation modeling (SEM).

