### Semi-structured interview

To investigate the social dimension of CRF, a semi-structured interview will be conducted (duration ~ 30 min). Demographic (e.g., age, gender, socio-professional category, residence area, income) and sociability (e.g., family, friendly, professional) will be addressed. The interview will be introduced by an open question on a typical week to then develop the sociability. The entire interview will be audio recorded, fully transcribed and then will be the subject of a lexicographical treatment for rating quantity and intensity of sociability (on a scale from − 5 to 5). In order to build a typology of patients’ sociability, researchers will also assess the level of social ties’ perception. Lastly, family, friendships, professional sociabilities and income will be considered in the SEM analysis.

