### Sample size

A sample size of *n* = 200 patients has been chosen on the basis of resource constraints [53]. 200 correspond to a 15% inclusion rate of the patients meeting the inclusion criterion during a 24 months inclusion period and including a 20% potential drop-out rate. Considering this sample size, a sensitivity power analysis performed with G-power (*F* tests family, linear multiple regression, *R*^*2*^ increase) to estimate the smallest effect size we could detect with 90% power regarding our main independent variable (i.e., CRF) at the level of analysis with the lowest power (i.e., level 2, between-person level). This analysis, with a power of 0.90, an α level of 0.05 and 6 predictors (i.e., 6 latent variables), revealed that the smallest effect size we could detect with 90% power, at this level of analysis, is *f*^*2*^ = 0.09, which correspond to a small to medium effect.

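### Education, named in the Background as a predictor of CRF, is not among the listed model variables, so the visit-wise and between-person Cognitive-to-CRF path may be confounded

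*Protocol article*

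**What the plan says.** The Background summarises the one longitudinal study that it credits with combining more than two dimensions of CRF. Only baseline results were available: "They reveal that younger age, lower educational level, lower disease stage and history of childhood maltreatment were found to be significant predictors of CRF". No effect size is given.

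The section on the semi-structured interview gives the demographic topics as examples: "Demographic (e.g., age, gender, socio-professional category, residence area, income) and sociability (e.g., family, friendly, professional) will be addressed". Education is not named. The same section then states which interview variables are modelled: "Lastly, family, friendships, professional sociabilities and income will be considered in the SEM analysis".

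The section on cognitive tests describes the MoCA as a plain sum ("The MoCA total score (/30) is obtained by summing the scores from each item") and fixes the three indicators: "For SEM analysis, MoCA total scores (/30), TMT time (s) and Stroop interference scores (%) will be considered". It states no norming or adjustment for education.

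Table 3 lists the latent and manifest variables. It contains cancer stage and income but no education variable. The Statistical analysis section plans cross-sectional models at each visit, then a longitudinal multilevel model, and deletes non-significant paths.

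**The concern.** Of the four predictors in the cited study, disease stage enters the model and education does not. A variable that both lowers cognitive test scores and raises CRF, and is left out, is credited to whichever modelled variable carries it. Here that could be Cognitive function. The path could then reach significance although cognition plays no part, and a rule that keeps significant paths would retain it. The Discussion expects the model to inform CRF management, so a stable difference in schooling could be read as a cognitive mechanism of fatigue.

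**Working it through.** **1. The plan's own figure.** The Sample size section uses N = 200, "with a power of 0.90, an α level of 0.05 and 6 predictors (i.e., 6 latent variables"), and reports a smallest detectable f² of 0.09. With the noncentral F distribution (noncentrality f² × N, 6 and 200 − 6 − 1 = 193 degrees of freedom), 90% power needs f² = 0.0900. The figure reproduces and is not at issue. The stated 20% drop-out leaves 200 × 0.80 = 160 women, so both sizes are used below.

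**2. Inputs for the bias.** None of these is in the document; all are assumptions.
- Three cognitive tests, coded so that higher is better, each loading 0.7 on the factor.
- Education correlates r = 0.3 to 0.5 with the cognitive factor.
- Education's own effect on CRF is b = −0.10 to −0.25 SD.
- Education correlates 0.3 with a social score that is in the model.
- The true cognitive effect on CRF is zero.

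**3. Formulae.** The sum of the three tests has variance 3 + 6 × 0.49 = 5.94. If k of the three tests depend on education:
- correlation of the cognitive score with education: a = k × 0.7 × r / √5.94
- correlation of the cognitive score with the social score: c = 0.3a
- expected cognitive coefficient with education omitted: b × (a − 0.3c) / (1 − c²)

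The rejection rate comes from the noncentral F with 1 degree of freedom at α = 0.05.

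Worked example with k = 3, r = 0.4, b = −0.20: a = 3 × 0.28 / 2.437 = 0.345; c = 0.103; coefficient = −0.20 × (0.345 − 0.031) / 0.989 = −0.063.

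**4. Results, all three tests depending on education.**

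| r | b | Bias (SD) | False positives, N = 160 | N = 200 |
|---|---|---|---|---|
| 0.3 | −0.10 | −0.024 | 6.0% | 6.3% |
| 0.4 | −0.15 | −0.048 | 9.2% | 10.2% |
| 0.4 | −0.20 | −0.063 | 12.5% | 14.5% |
| 0.5 | −0.25 | −0.100 | 24.0% | 28.9% |

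Simulation with 1,500 replicates per cell agrees. At N = 200 the three lower rows gave 10.1%, 15.3% and 27.7%, falling to 4.9%, 5.9% and 5.1% with education in the model.

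**5. Fewer tests depending on education** (N = 200, r = 0.4, b = −0.20). Two tests: bias −0.042, rate 9.1%. One test: bias −0.021, rate 6.0%. If no test depends on education, the rate stays at 5%.

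**6. Does income cover it?** This was checked on a separate grid, in which education correlates directly with the cognitive score and with CRF, and income correlates 0.5 with education (also assumed). At N = 200:

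| Education–score / education–CRF | Neither modelled | Income modelled | Education modelled |
|---|---|---|---|
| 0.2 / 0.1 | 5.9% | 5.5% | 5.0% |
| 0.4 / 0.2 | 20.4% | 14.0% | 5.0% |
| 0.5 / 0.3 | 56.9% | 38.4% | 5.0% |

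Income reduces the excess but does not remove it. The last row goes beyond the range in step 2 and shows how strongly the rate depends on the assumptions.

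All rates are for a composite score in a linear regression, not the full latent model with its Physical, Biological and Emotional factors. They are approximate.

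**The case against.** The strongest reply is that confounding needs two links and the document supplies only one. Nothing in it says that the MoCA, TMT or Stroop scores depend on education. A reader might infer that all three certainly do. The document does not support that, and it is least secure for Stroop interference, which is built from the woman's own times across three parts. This stands: the size is conditional, and its lower end is close to the nominal 5%.

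The link to CRF is also thin: one study, baseline results only, no effect size. Applying it to every visit is a further assumption. If education acted on CRF only through cognition, leaving it out would cause no bias.

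A reader might also infer that education is not collected. The demographic list is introduced as examples, in an article that condenses a fuller protocol, so this is not shown.

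Another reply is that covariates are usually left to the analysis plan, and that the Discussion admits that not every relevant parameter can be measured. That covers unstated detail. It does not fully answer the point, because the article itself states which interview variables and cognitive scores enter the model, and the relevant parameters that it says were excluded are pain and nutrition, given as examples; education is not mentioned.

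Finally, the study is longitudinal, and a characteristic that is essentially fixed over 18 months cannot confound within-person change. This is correct and limits the scope.

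**Conclusion.** The point holds in a limited form. What is firm is that education is named as a predictor of CRF, is absent from the listed SEM variables, and is not adjusted for in the stated cognitive scores. What is conditional is the consequence. If the scores depend on education and education has its own effect on CRF, the Cognitive-to-CRF path is biased towards worse cognition going with more CRF, by about −0.02 to −0.10 SD. The false-positive rate is then about 5 to 30% at 160 to 200 women, and about 6 to 9% in the middle of the range if only one or two tests are affected.

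This concerns the per-visit models and the between-person level, which is the level at which the plan calculated its power. It would be wrong to conclude that every Cognitive-to-CRF path is compromised, since the within-person path is not affected. Nor is it shown that a significant cognitive path would be false.

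**What to change.** Confirm that highest educational level is recorded at visit 1, and add the question if it is not. Regress both Cognitive function and CRF on it in each per-visit model and at the between-person level of the longitudinal model. If education cannot be obtained, use socio-professional category, which the interview already covers, as a partial proxy and say that it is one.

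The cost is at most one interview question and a few extra parameters in the model.

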### Postural tests

Participants will be asked to stand up barefoot, as still as possible, during 60 s on a pressure distribution measurement platform (FDM-S, zebris Medical GmbH, Isny, Germany). Feet position will be standardized using markings to keep both heels spaced apart by 10 cm and an angle of 15° between both feet. Participants will be advised to keep arms alongside the body during recording. Four conditions composed of two trials of a simple task and two trials of a dual task (counting backwards by 2 from a number close to 100) with eyes open or closed will be counterbalanced and interspersed with a 2 min rest period. In eyes open conditions, participants will be asked to stare at a visual marker placed 2 m in front at eye level. For the dual task, participants will be asked to count as fast as possible whilst remaining as immobile as possible. The numbers of answers and errors will be recorded. Temporal analysis will be performed in order to investigate anterior-posterior and medial-lateral center of pressure (COP) distance, mean and maximal COP velocities and 95% confidence ellipse area. In addition, the frequency domain measures (relative power in < 0.5 Hz; 0.5–1.5 Hz; > 1.5 Hz frequency bands) will be computed. 95% confidence ellipse area (mm^2^) will be considered in the SEM to represent the physical function latent variable, while maximal COP velocities (mm/s) will be considered representative of the emotional function latent variable, as it is a relevant hallmark of depression-related psychomotor retardation [44].

### Neuromuscular fatigability test

Throughout this test, participants will remain in prone position on a patient table, with a fully-extended knee and an ankle angle of 90°, their foot securely blocked at the metatarsal level in a custom–made device enabling isometric strength measurement with a load cell (LSB350, Futek, Irvine, USA). Firstly, optimal electrical stimulation intensity will be determined to set the supramaximal intensity used during the subsequent neuromuscular assessments by progressively increasing the current (from 20-mA to 200-mA, with a 20-mA increment) until there is no further increase in the evoked isometric twitch response. The last intensity obtained will be further increased by 20% to ensure stimulus supramaximality. All electrical stimulations will be delivered with a constant current (Digitimer DS7A-H, Hertfordshire, UK) using square-wave stimuli of 200 μs duration with a maximal voltage of 400-V and via rectangular self-adhesive electrodes (5 × 10 cm, Compex). The cathode will be placed over the gastrocnemii (~ 5 cm distal to the popliteal fossa) and the anode over the soleus (~ 10 cm proximal to the calcaneus). Secondly, participants will accomplish a standardized warm-up (10 isometric contractions of 4 s at 50% of their maximal strength with 4 s of recovery in between), followed by 2-min of rest and then by the maximal voluntary contraction (MVC) measurement (two MVC of 4 s separated by 2 min; if the difference between these MVCs is superior to 5%, a third one will be performed). The higher peak force produced will be considered as the MVC in non-fatiguing conditions. Next, pre-fatigue neuromuscular functions will be assessed on a third MVC, using a 100-Hz doublet during the force plateau and a stimulation sequence on the relaxed muscles beginning 2 s after the end of contraction: a 100-Hz doublet, a 10-Hz doublet and a simple stimulation, interspersed by 3 s. The fatiguing exercise will be composed of 62 isometric MVC in ankle plantar flexors with the dominant leg (Fig. 2). Each MVC will last 4 s with 1 s rest; duty cycle will be ensured using a metronome with visual and sound signals. To avoid pacing strategies, participants will not be informed of the time remaining or the number of MVC performed [45]. Investigators will use verbal encouragements for participants to contract as strong as possible during MVC. The post-fatigue neuromuscular functions will be assessed on the last MVC of the fatiguing exercise (62nd) with the same stimulation procedure as in pre-fatigue condition. On the 60th MVC, neuromuscular functions will also be tested but only with two 100-Hz doublets (during the force plateau and on the relaxed muscles 2 s after the MVC end).

**Fig. 2 Fig2:**
[figure not shown]
Schematic illustration of the fatiguing exercise and neuromuscular assessments. ↓ represents electrical stimulation

Peak force occurring during each 4-s MVC set will be recorded and the force-time relationship asymptote (F_A_; expressed in percentage of the MVC in non-fatiguing conditions) will be used to represent a neuromuscular fatigability threshold, above which fatigability drastically sets in [20, 46, 47]. Then, voluntary activation (VA) and evoked forces by a 100-Hz doublet (Db100) will be determined using the interpolated twitch technique [48] and expressed in pre-post fatiguing test differences, normalized to pre-fatiguing test values. F_A_ (% MVC), VA (%) and Db100 (%) will be considered in the SEM.

### Cardiorespiratory fitness test

After a five-minute recovery period, a blood drop (10 μL) will be taken from the earlobe and analyzed extemporaneously (within 15 s) to obtain a resting blood lactate concentration ([Lactate]_b_) (Lactate Scout 4, EKF diagnostics, Cardiff, UK). Then, participants will perform a submaximal incremental exercise on a cycle ergometer (model 928E, Monark, Varberg, Sweden), with saddle and handlebar heights adjusted for each patient. Throughout the test, participants will be encouraged to maintain a constant cadence (approximately 60 rpm) and heart rate (HR) will be recorded with a heart rate monitor (HRM-Dual, Garmin, Olathe, USA). After a 3-min standardized warm-up at a rate of perceived exertion (RPE) of 8–9 (Borg 6–20 scale), the test will start at 20 W. Every 2 min [Lactate]_b_ will be measured as previously described and then intensity will be increased by 10 W steps. Just before the end of the step, participants will indicate RPE (Borg 6–20 scale). Exercise will be stopped as soon as i) [Lactate]_b_ ≥ 4 mmol. L^− 1^; ii) participant RPE > 15; or iii) participant will no longer be able to maintain the 60 rpm cadence. Participants will be able to interrupt the exercise when they wish to do so, particularly in the case of nausea, chest pain or dyspnea. This test will be used to determine the physiological and biomechanical parameters (i.e., HR, power output associated with the first lactate threshold (LT1; defined as the first inflection point in the lactate concentration ([Lactate]_b_) curve). Power output at LT1 (W) will be considered in the SEM.

### Clinical and biological data

As experimental sessions will accompany medical follow-ups, clinical and biological data will be also recorded. Cancer stage and details related to treatments (e.g., type, duration and dose) will be recorded in a medical file by their oncologist. Venous blood samples will be collected by medical staff. Plasma will be obtained after a 10 min centrifugation at 4 °C, then divided into aliquots and stored at − 80 °C until analysis. Following assays will be performed on plasma for the assessment of inflammation (IL-6, TNFɑ, IL-8, IL-1β). Abdominal computed tomography (CT) images at the L3 level will be taken by medical staff on two occasions (Visit 1 and Visit 2). The surface of the muscular tissues will be selected according to the CT Hounsfield unit and normalized to stature in order to calculate the lumbar skeletal muscle index (LSMI). A cut-off value (LSMI < 38.5cm^2^/m^2^) will be used to characterize sarcopenia [49]. Cancer stage and treatment; sarcopenia; and IL-6, IL-1β, TNFɑ (pg/mL) concentrations will be considered in the SEM.

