### Statistical analysis

Hypotheses will be addressed by constructing a biopsychosocial model of the relationships among biological, physical, emotional, cognitive and social dimensions of CRF using multilevel SEM. SEM is particularly well-suited to this type of analysis because it simultaneously accounts for multiple interactive relationships among variables, easily handles multiple sources of variance, and permits testing of hypothesized directional relationships [54, 55]. Consequently, the results of SEM analyses facilitate inferences regarding the relationships among variables [56]. Relations between the manifest variables and their underlying latent constructs in a hypothesized biopsychosocial model predicting CRF are presented in Table 3. The model will be tested with the maximum likelihood method using Lavaan *R* package for SEM [57]. A primary cross-sectional analysis will be completed using data collected at each visit, and then subsequently by using the longitudinal data set. The models’ fit was assessed by examining the minimum discrepancy (CMIN/DF), the probability level (*p*-value), the Bentler-Bonett normed fit index (NFI), the comparative fit index (CFI), the Tucker–Lewis-Index (TLI), and the root-mean-square error of approx- imation (RMSEA). A satisfactory model fit is indicated by a CMIN/DF ratio below 2.00 [58], a *p*-value over 0.05 [59], a NFI over 0.95 [60], a TLI over 0.90 [61], a CFI over 0.93 [62], and a RMSEA below 0.05 [63]. All non-significant paths were deleted according to the methods described by MacCallum [64].

**Table 3 Tab3:** Latent and manifest variables included in the model built by SEM

Latent variable	Manifest variable	Test
**Social function**	Family sociability	Semi-structured interview
	Friendly sociability	Semi-structured interview
	Professional sociability	Semi-structured interview
	Income	Semi-structured interview
**Cognitive function**	MoCA total score	MoCA
	TMT time	TMT
	Interference score	Stroop
**Physical function**	95% confidence ellipse area	Postural test
	F_A_	Neuromuscular fatigability test
	VA	Neuromuscular fatigability test
	Db100	Neuromuscular fatigability test
	Power output at LT1	Cardiorespiratory fitness test
	Sleep efficiency	Actigraphy
	Total activity duration	Actigraphy
	Sarcopenia	Abdominal CT at the L3 level
**Biological function**	Cancer stage	Medical file
	Cancer treatment	Medical file
	IL-6 concentration	Blood sample
	IL-1β concentration	Blood sample
	TNFɑ concentration	Blood sample

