## Discussion

American and European guidelines [65–67] recommend screening for CRF using self-reported questionnaires [68]. Even though this method remains simple and easily feasible for both clinician and patients, this assessment method does not enable the understanding and management of underlying mechanisms. Despite that CRF has been studied for decades, and recent studies have recognized that CRF is multifactorial and may be influenced by a variety of mechanisms [8, 38, 69], few longitudinal and multidimensional studies have been implemented. This is one of the main obstacles to the assessment and management of CRF. Therefore, our longitudinal study is designed to build a model by examining longitudinally biopsychosocial correlates of CRF.

The greatest challenge in designing this study was to select the most pertinent and suitable parameters/variables for each of the biopsychosocial dimensions in order to remain feasible for fragile patients. As it is not possible to measure all parameters potentially involved in CRF, we had to exclude some dimensions such as pain or nutrition that would have otherwise been pertinent [34, 70]. All parameters included are among those most related to CRF, according to the literature.

All patients with localized breast cancer will be included, inherently incorporating various conditions of cancer stages and treatment. Although this may result in a high level of variability and statistical noise, we deemed it necessary to build a real life model that can be later used in clinical practice. Furthermore, with a prevalence up to 50% for CRF [2], it is reasonable to believe that a proportion of participants will not be suffering from clinically important CRF. This could be perceived as a limitation when studying CRF. However, because clinical relevance is based on cut-off values, some patients could potentially be misclassified and we think that CRF should be understood as a continuum. Moreover, even mild CRF can have an impact on patient quality of life.

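### CT muscle index enters the model only as a thresholded sarcopenia variable, losing at least a third of that indicator's cross-sectional information and most of its information on change; continuous LSMI is already available

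*Protocol article*

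**What the plan says.** Clinical and biological data: muscle area on the L3 CT slice is "normalized to stature in order to calculate the lumbar skeletal muscle index (LSMI"), a continuous quantity in cm²/m². The scans "will be taken by medical staff on two occasions (Visit 1 and Visit 2"). A single cut-off, LSMI < 38.5 cm²/m², "will be used to characterize sarcopenia". The variables passed to the model are then listed: "Cancer stage and treatment; sarcopenia; and IL-6, IL-1β, TNFɑ (pg/mL) concentrations will be considered in the SEM". The cytokines carry a unit, sarcopenia carries none, and LSMI is not in the list.

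Statistical analysis, Table 3: Sarcopenia is a manifest variable of Physical function, with "Abdominal CT at the L3 level" as its source. The other seven indicators of that factor are ellipse area, F_A, VA, Db100, power output at LT1, sleep efficiency and total activity duration, all continuous. On estimation: "The model will be tested with the maximum likelihood method using Lavaan". No method for categorical indicators is named.

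Two other measures with quoted cut-offs are handled differently. MoCA has a cut-off of 26, but the total score out of 30 goes into the SEM (Cognitive tests). The fatigue score has a threshold of 39, but the degree of CRF in % goes in (Participant-reported outcomes).

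**The concern.** LSMI has to be computed before the cut-off can be applied, so the continuous value will exist for every scan. Passing on only which side of 38.5 a woman falls treats all women below the line as alike, and all women above it as alike.

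Two things are at stake for this indicator. At a single visit, its correlation with anything linearly related to muscle mass is attenuated. Across the two scans, a woman who loses muscle but stays on the same side of 38.5 is recorded as unchanged, in a study whose stated purpose is longitudinal. In addition, maximum likelihood under the usual normal model treats a 0/1 variable as if it were continuous and normal.

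**Working it through.** **The plan's own figure.** The only statistical figure in the article is the smallest detectable effect, f² = 0.09 (Sample size: N = 200, 6 predictors, α = 0.05, power 0.90). A noncentral F with 6 and 200 − 6 − 1 = 193 degrees of freedom and noncentrality f²·N gives f² = 0.0900. It reproduces and does not depend on how sarcopenia is coded, so this point leaves it untouched.

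**Inputs from the article.** Cut-off 38.5 cm²/m²; CT at 2 of 4 visits; one of eight Physical function indicators; maximum likelihood. **Not in the article, so assumed:** normal LSMI, a linear relation to the factor, prevalence below the cut-off, and stability between visits.

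**Cross-section.** If a normal variable is cut so that a proportion p lies below the cut, its correlation with any linearly related variable is multiplied by r = φ(z_p)/√[p(1 − p)]. The share of linear information kept is r². At p = 0.20, for example, z = −0.842, φ(z) = 0.280 and √(0.2 × 0.8) = 0.4, so r = 0.70 and r² = 0.49.

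| Prevalence | r | Kept (r²) | Lost |
|---|---|---|---|
| 50% | 0.798 | 64% | 36% |
| 40% | 0.789 | 62% | 38% |
| 30% | 0.759 | 58% | 42% |
| 20% | 0.700 | 49% | 51% |
| 10% | 0.585 | 34% | 66% |

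The smallest possible loss is 36%, at 50% prevalence. The loss passes half only when prevalence is below about 21% or above about 79%. As an illustration, an assumed mean LSMI of 40-45 with SD 6-7 puts 14-42% of women below 38.5 and gives a loss of 37-59%.

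**Change from visit 1 to visit 2.** Pairs of LSMI values were simulated, and the change in LSMI was correlated with the change in the flag. The loss is 1 − r².

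- Wide assumptions (prevalence 10-50%, between-visit correlation 0.80-0.95, mean shift 0 or −0.2 SD): the flag changes in 4-21% of women, r² is 0.07-0.31, and the loss is 69-93%.
- Narrower assumptions (mean 40-45, SD 6-7, mean loss 3-5%, SD of change 4%): the flag changes in 7-15% of women. Of women losing 5% or more, 78-86% show no change in the flag. The correlation is 0.20-0.33 in absolute value, so the loss is 89-96%. These inputs imply a between-visit correlation of about 0.95-0.97, at or beyond the stable end of the wide range.

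Together the loss is about 70-95%, and higher when muscle mass is more stable.

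**Reach into the factor.** Assume eight equal loadings and attenuate one of them by 0.798 to 0.585. Write S for the sum of λ²/(1 − λ²) over the indicators. The squared determinacy of the factor is then S/(1 + S). It falls from 0.604 to 0.591-0.582 at loading 0.4, from 0.727 to 0.716-0.708 at 0.5, and from 0.885 to 0.878-0.874 at 0.7. That is about 1 to 2 points.

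**The case against.** The strongest reply is that the effect on the study's target is small. Seven of the eight indicators are untouched, and a noisier reflective indicator mainly lowers its own loading. This stands: the factor-level illustration gives only 1-2 points. The percentages above describe one indicator and must not be read as a loss in the model's explained variance.

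A second reply is that the article never uses the word binary and is a condensed account, so the coding may be set elsewhere. This stands in part. However, the variable is named in two places, without a unit and directly after a cut-off, and LSMI is in neither list. If continuous LSMI was intended, both places still name the wrong variable and need the same edit.

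Third, the Background names sarcopenia itself as a CRF correlate, so a clinically defined variable follows the stated hypothesis. That is fair, and the flag is less efficient only if the relation is roughly linear, which is an assumption here. Nor is the mismatch with maximum likelihood peculiar to sarcopenia: cancer stage and treatment are categorical indicators too.

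A reader might also infer that the Discussion forbids this practice, since it says that "because clinical relevance is based on cut-off values, some patients could potentially be misclassified and we think that CRF should be understood as a continuum". It does not go that far. The sentence concerns CRF, the outcome, and defends including women without clinically important fatigue; it says nothing about thresholding covariates.

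**Conclusion.** The point holds as a cheap improvement. As written, a continuous index is reduced to a threshold variable before it enters the SEM, whereas MoCA and the fatigue score enter as scores. Under normality and linearity, the flag loses at least about a third of this indicator's cross-sectional information, and most of its information on the visit 1 to visit 2 change (about 70-95% over the assumed stability). It also fits poorly with plain maximum likelihood.

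Two stronger readings are tempting. One is that most of the cross-sectional information goes; that needs a prevalence below about 21% or above about 79%, and the article gives none. The other is that nearly all the within-woman information goes; that rests on an assumed SD of change, or an equally high between-visit correlation, which the article does not give either. No material effect on the path to CRF has been shown, and the f² = 0.09 calculation is unaffected.

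**What to change.** In Clinical and biological data and in Table 3, replace sarcopenia with continuous LSMI (cm²/m²) as the manifest variable wherever CT is available. Keep the existing cut-off for describing the cohort; its clinical value is not questioned here. If the flag is kept in the model, name an estimation method suited to categorical indicators.

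The cost is one wording change in two places, with no new scans, patients or visits. The downside is that the model would no longer estimate a loading for clinically defined sarcopenia itself.
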